#### Protocol

Subjects will visit the university twice and during each visit they will stay in the respiration chamber for two days and nights (36hrs). During one of these visits subjects will test the treatment condition (green tea; 757 mg/capsule [84.5 mg EGCG + 2.1 mg caffeine], 3 capsules with each breakfast and dinner) and the other visit they will test the placebo condition (soy oil; 757 mg/capsule, 3 capsules with each breakfast and dinner). Subjects receive a glass of water in order to swallow the capsules more comfortably. Both visits are separated by a period of 4 weeks, which will prevent influences of the previous experiment and influences of differences in menstrual cycle phase on energy expenditure. The respiration chamber experiment starts in the evening of day 1 at 19:00h and ends at 07:00h on day 3.

#### Indirect calorimetry

Oxygen consumption and carbon dioxide production will be measured in the respiration chamber [21]. The respiration chamber is a 14 m^3 hotel room, furnished with a bed, chair, computer, television, radio, dvd-player, telephone, intercom, sink and toilet. The room is ventilated with fresh air at a rate of 70-80 l/min. The ventilation rate is measured with a dry gas meter. The concentrations of oxygen and carbon dioxide will be measured using a paramagnetic O2 analyzer and an infrared CO2 analyzer. During each 15-min period six samples of outgoing air for each

chamber, and one sample of fresh air, zero gas, and calibration gas will be measured. The gas samples to be measured will be selected by a computer that also stores and processes the data [21].

#### Energy expenditure and substrate oxidation

24-h energy expenditure consists of sleeping metabolic rate (SMR), diet-induced energy expenditure (DEE), and activity-induced energy expenditure (AEE). 24-h energy expenditure and 24-h respiratory quotient (RQ) will be calculated from 19:00h on day 1 to 07:00h on day 3, using the formula of Brouwer [22]. Physical activity is monitored using a radar system working on the Doppler principle. SMR is defined as the lowest mean energy expenditure measured over three consecutive hours between 00:00h and 07:00h. DEE will be calculated by plotting energy expenditure against radar output, both averaged over 30-min periods. The intercept of the regression line at the lowest radar output represents the energy expenditure in the inactive state (Resting Metabolic Rate; RMR), consisting of SMR and DEE [23]. DEE will be determined by subtracting SMR from RMR. Activity-induced energy expenditure will be determined by subtracting RMR from 24-h energy expenditure. The Physical Activity Level (PAL) will be calculated by dividing 24-h energy expenditure by SMR. Carbohydrate, fat, and protein oxidation will be calculated using  $O_2$  consumption and  $CO_2$  production, deuterium labelled palmitic acid and urinary nitrogen excretion, with the formula of Brouwer [22].

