### **Sample size**

The primary parameter is total energy expenditure. Dulloo *et al.* [13] report TEE values of  $9867 \pm 488$  kJ/day and  $9538 \pm 521$  kJ/day for green tea vs placebo [13]. With an  $\alpha$  of 0.05 and  $\beta$  of 0.10 (power=1- $\beta$ =0.90) the number of subjects needed is:

$$N = 21 \times (SD)^2 / (\text{mean1} - \text{mean2})^2 + 0.96$$

$$N = 21 \times (488)^2 / (9867 - 9538)^2 + 0.96$$

$$= 47 \text{ subjects needed}$$

Rounded up, 48 subjects will be included in the experiment which means that each group contains 12 subjects. When taking drop outs into account 193 persons need to be screened. For the Asians with the COMTH allele 17 people have to be screened to get 12 subjects, as the allele frequency is 70%. The allele frequency for the COMTL allele is 15%, which means that 80 people have to be screened. In Caucasians for either the COMTL allele as well as for the COMTH allele 48 people have to be screened, as the allele frequencies are 25%. In total this would mean that 193 subjects have to be screened in order to find 48 subjects. This is an obtainable number since habitual high coffee drinkers do not apply for entering the study as the poster and advertisements mention the inclusion criteria. Also, coffee consumption in Asian people is rather low compared with Caucasians.

An ANOVA repeated measures with post-hoc tests will be used to compare the effects of green tea on TEE and fat oxidation in subjects with different ethnicity and different COMT polymorphisms. A p-value <0.05 will be regarded as statistically significant.

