#### Urine collection

Urine will be collected from 19.00h day 1 till 07.00h day 2, 07.00h day 2 till 19.00h day 2, and 19.00h day 2 till 07.00h day 3. Samples will be collected in containers with 10 ml H2SO4 to prevent nitrogen loss through evaporation. The subjects will be told, before entering the respiration chamber, to handle the urine containers with the most caution because of the presence of H2SO4. Volume and nitrogen concentration will be measured, the latter using a nitrogen analyzer.

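### The 24-h energy expenditure, the primary parameter, and the 24-h RQ are calculated over a 36-hour window of two nights and one day, with no rule for reducing it to 24 hours

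*Protocol*

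**What the plan says.** The Sample size section names the endpoint: "The primary parameter is total energy expenditure". It plans on a difference in kJ/day, 9867 against 9538.

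The section Energy expenditure and substrate oxidation fixes the calculation window: "24-h energy expenditure and 24-h respiratory quotient (RQ) will be calculated from 19:00h on day 1 to 07:00h on day 3". The Protocol subsection gives the same start and end for the whole stay: "The respiration chamber experiment starts in the evening of day 1 at 19:00h and ends at 07:00h on day 3". It also gives the length, since at each visit "they will stay in the respiration chamber for two days and nights (36hrs"). Urine collection divides the same span into three 12-hour blocks: "19.00h day 1 till 07.00h day 2, 07.00h day 2 till 19.00h day 2, and 19.00h day 2 till 07.00h day 3".

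Sleeping metabolic rate is defined by clock time only: "SMR is defined as the lowest mean energy expenditure measured over three consecutive hours between 00:00h and 07:00h". From these quantities the protocol derives DEE (RMR minus SMR), AEE (24-h energy expenditure minus RMR) and PAL (24-h energy expenditure divided by SMR).

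The treatment is given as "3 capsules with each breakfast and dinner". Neither the Protocol subsection nor Energy intake gives clock times for meals, and neither says whether a dinner with capsules is taken on day 1.

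**The concern.** A quantity labelled 24-h is calculated over 36 hours, and nothing says how one becomes the other. This is more than a detail that an analysis plan might add later, because the protocol does fix the window and the window conflicts with the name of the variable.

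Three things are at stake.

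- **Level.** A 36-hour sum is not a daily value. A 36-hour mean counts the night twice and the day once. PAL and AEE are built on the result, and RQ and substrate oxidation are weighted towards the night in the same way.
- **SMR.** The 00:00-07:00 period occurs twice in the stay, and no night is named. The choice carries into DEE and PAL.
- **Contrast.** The first 12 hours come before the only breakfast inside the window. If they are untreated, they enter the green tea condition without any green tea effect.

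Sum, rescaled mean and sub-window are all compatible with the text, so the choice could be made after the data are seen.

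**Working it through.** **Inputs.** Window 19:00 day 1 to 07:00 day 3 (Energy expenditure and substrate oxidation). Green tea 9867, placebo 9538, SD 488 kJ/day, alpha 0.05, power 0.90 (Sample size). The night/day rates and the split of the effect over the day are assumptions; the protocol gives neither.

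**1. The plan's own figure.** 21 × 488² / 329² + 0.96 = 47.16, so the stated 47 is reproduced. The planning effect is 9867 − 9538 = 329 kJ/day.

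**2. Length of the window.** 5 h (19:00-24:00, day 1) + 24 h (day 2) + 7 h (day 3) = 36 h.

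**3. Weight of the night.**

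| Hours | In the 36-h window | In a true 24 h |
|---|---|---|
| 19:00-07:00 | 24/36 = 66.7% | 12/24 = 50% |
| 00:00-07:00 | 14/36 = 38.9% | 7/24 = 29.2% |

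**4. Level if the 36 hours are averaged and rescaled.** Let the night rate be r times the day rate, with h night hours per day. The ratio to a true 24-h value is [(2hr + 36 − 2h)/36] / [(hr + 24 − h)/24].

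- h = 7, r = 0.9: 0.9611 / 0.9708, a fall of 1.0%, or 96 kJ/day on 9538.
- h = 12, r = 0.6: 0.7333 / 0.8, a fall of 8.3%, or 795 kJ/day on 9538.
- Night at 1.1-1.2 and day at 1.5-1.6 times SMR, averaging 1.35: (2 × 1.2 + 1.5)/3 = 1.300 and (2 × 1.1 + 1.6)/3 = 1.267, against 1.35. The fall is 3.7% to 6.2%.

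**5. Level if the 36 hours are summed.** At a constant rate the sum is 36/24 = 1.5 times the daily value (9538 becomes 14307). With the last set of rates in step 4 it is 1.5 × 0.938 to 1.5 × 0.963, or 1.41 to 1.44. PAL would be inflated by the same factor, and AEE would set a 36-hour total against RMR.

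**6. Contrast, rescaled to 24 h.** Let the effect over 07:00-07:00 be 329 kJ, split into D by day and N by night. If the first 12 hours are undosed, the 24-h effect is (D + N) × 24/36. If they are dosed as the second night is, it is (D + 2N) × 24/36. The last column puts each effect into the protocol's formula with SD 488.

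| Assumption | Effect, kJ/24 h | Ratio to 329 | N by the protocol's formula |
|---|---|---|---|
| First 12 h undosed, any split | 219.3 | 0.67 | 104.9 |
| First night dosed, effect all by day | 219.3 | 0.67 | 104.9 |
| First night dosed, 75% by day | 274.2 | 0.83 | 67.5 |
| First night dosed, 60% by day | 307.1 | 0.93 | 54.0 |
| First night dosed, 50% by day | 329.0 | 1.00 | 47.2 |
| First night dosed, one third by day | 365.6 | 1.11 | 38.4 |

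**7. What the N column means.** The formula is of the two-sample type (2 × (1.960 + 1.282)² ≈ 21), while the trial is a crossover. The column therefore shows relative loss only. As a paired comparison of 48 subjects with SD 488 in each condition and an assumed within-subject correlation ρ, the SD of the difference is 488 × √(2(1 − ρ)). At 219.3 kJ the power is 0.58 for ρ = 0, 0.86 for ρ = 0.5 and 0.98 for ρ = 0.7.

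**8. A true 24-h window.** 07:00 day 2 to 07:00 day 3 restores the 50/50 split and leaves the planning effect at 329 kJ/24 h and N at 47.

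**The case against.** The best reply is that the same window applies in both conditions of a crossover. Extra night hours shift both levels together, and a common shift does not by itself bias the within-subject contrast. That stands. It answers the worry about direction of bias. It does not make the reported value a 24-h value, and it does not repair PAL or AEE.

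A reader might infer that the window dilutes the green tea effect as a matter of course. The protocol does not support that. Dilution needs an undosed first night or an effect that falls mainly by day, and neither is stated. Capsules at a day-1 dinner are neither described nor excluded. With a dosed first night and an even effect nothing is lost, and with an effect mainly at night the contrast grows.

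A reader might also infer that the trial has only about 58% power. That needs the undosed case, no correlation between two measurements in the same person, and an SD that stays at 488 in a different window. It also concerns the green tea main effect only.

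The inflated PAL arises only if a 36-hour total is actually used, which the protocol does not say. The 1 to 8% rests on assumed rates. DEE is RMR minus SMR and does not use the 24-h total, so it inherits only the uncertainty over which night supplies SMR. RQ is affected but is not the primary parameter.

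**Conclusion.** The point holds for the definition of the endpoint, and this must be corrected before analysis because it concerns the primary parameter. The 24-h label contradicts the 36-hour window, no reduction rule is given, and neither a sum nor a rescaled mean over that window is a true 24-h value. The misweighting, 66.7% of the weight on 19:00-07:00 instead of 50%, follows from the protocol's own clock times without any assumption.

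The consequences in kJ are conditional. The level error is about 1 to 8% downwards for a rescaled mean, under assumed night/day rates, or a factor of about 1.4 to 1.5 upwards for a sum. The ratio of the contrast to its planned size runs from 0.67 to about 1.11 over the cases examined, depending on day-1 dosing and on when the effect occurs. Loss of the green tea contrast is thus a possibility that the protocol leaves open and cannot be claimed as a result.

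**What to change.** In Energy expenditure and substrate oxidation, define 24-h energy expenditure, RQ and substrate oxidation over one true 24-hour window, 07:00 on day 2 to 07:00 on day 3. The last two urine nitrogen collections, "07.00h day 2 till 19.00h day 2, and 19.00h day 2 till 07.00h day 3", cover exactly these hours. State that SMR comes from the second night, and treat 19:00 day 1 to 07:00 day 2 as acclimatisation.

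Reconcile the Protocol, Energy expenditure and substrate oxidation, and Energy intake sections so that they state whether capsules are taken at dinner on day 1 and at what times meals fall. What the dosing should be is not a matter for this review.

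An explicit time-of-day weighting of all 36 hours would also give a 24-h value, but it needs more text, and its contrast would still depend on the day-1 dosing.

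The cost is a short amendment to the text and no new measurement. The first 12 hours leave the primary value; if they prove to be dosed, some treated data are set aside.

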#### Fat oxidation

Deuterium labelled palmitic acid (Cambridge Isotope, Andover, MA): d31-palmitic acid (DLM-215) was 98 atom%. This palmitic acid (20mg/kg body weight) is added to tomato juice and consumed at breakfast. Usually chocolate milk is used but recently we have published that the effect of green tea is not always present in combination with milk [24]. Tomato juice contains catechins as well, although in low amounts. The main antioxidant in tomato is besides vitamin C, lycopene. This antioxidant has just like catechins from green tea a beneficial effect on cancer. It does not affect energy expenditure and substrate oxidation such as the catechins from green tea. There is no EGCG, which is the most active form in green tea, present in tomatoes [25]. Therefore tomato juice will not influence the results. Also, when the juice is given in both conditions the difference in outcome parameters between both conditions remains the same. When subjects dislike tomato juice a different juice can be

selected for dissolving the palmitic acid. Urine samples will then be collected every 2 hours from 07.00h day 2 till 19.00h day 2 [26]. The product information for the palmitic acid can be found in the attachments. It is a product that is suitable for human consumption as it is already used in several studies [27-29], also in a previously by the medical ethical committee approved study (MEC 06-3-051).

#### Urine collection

Urine will be collected from 19.00h day 1 till 07.00h day 2, 07.00h day 2 till 19.00h day 2, and 19.00h day 2 till 07.00h day 3. Samples will be collected in containers with 10 ml H2SO4 to prevent nitrogen loss through evaporation. The subjects will be told, before entering the respiration chamber, to handle the urine containers with the most caution because of the presence of H2SO4. Volume and nitrogen concentration will be measured, the latter using a nitrogen analyzer.

#### Energy intake

During their stay in the chamber subjects will be fed in energy balance. Subjects receive their breakfast, lunch and dinner, at regular time points. The energy content of the food will be calculated using the equation of Harris-Benedict [30] that calculates Basal Metabolic Rate (BMR). BMR will be multiplied by an activity index of 1.35. Energy intake will be divided over the meals as 20% for breakfast, 40% for lunch, and 40% for dinner. The macronutrient composition of the diet will be 12/55/33 En% (protein/carbohydrate/fat). The diet will consist of normal food products, available in the supermarket. The actual diet will be determined in consultation with the subjects. They can indicate which food products they dislike and based on this information a diet will be composed with the abovementioned macronutrient composition. All foods will be prepared in a research kitchen from the Department of Human Biology by one of the researchers.

#### Questionnaires

The appetite profile will be scored every hour by the following anchored 100 mm Visual Analog Scales: How hungry/satiated/full/thirsty are you? (Anchors: not at all; very much); How is your desire to eat? (Anchors: very little; very large) [31].

#### Information about capsules

The product information for the green tea capsules can be found in the attachments.

For the placebo capsules there is no direct product information available, the product information from Gelkaps is used for placebo and green tea capsules. When specifying the placebo capsules the green tea extract is replaced with soy oil. The placebo thereby consists for 100% of soy oil. Soy oil is a globally consumed plant oil, and often used as a food additive and has hardly any flavour. Lecithin, which is also present in very small amounts in the capsules, is a product of soy oil after processing. It works as an emulsifier. These capsules have already been used in a previous study (NL19702.068.07/ MEC 07-3-080) and been approved by the medical ethical committee.

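### The soy-oil placebo supplies more fat than the green tea capsule, and the diet section makes no provision for it: the excess is 0.5 to 4.5 g/day and bears on the fat oxidation comparison only

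*Protocol*

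**What the plan says.** The subsection headed Protocol, under Methods and measurements, gives the two capsule regimens:

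- Active: "green tea; 757 mg/capsule [84.5 mg EGCG + 2.1 mg caffeine], 3 capsules with each breakfast and dinner".
- Placebo: "soy oil; 757 mg/capsule, 3 capsules with each breakfast and dinner".

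Information about capsules explains how the two differ: "When specifying the placebo capsules the green tea extract is replaced with soy oil". It concludes: "The placebo thereby consists for 100% of soy oil". The rest of the active capsule's content is left to a product sheet: "The product information for the green tea capsules can be found in the attachments".

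Energy intake sets food energy at Harris-Benedict basal metabolic rate times 1.35, split 20/40/40% over breakfast, lunch and dinner. It then fixes the composition: "The macronutrient composition of the diet will be 12/55/33 En% (protein/carbohydrate/fat"). It adds: "The diet will consist of normal food products, available in the supermarket". Capsules do not appear in that section.

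Fat oxidation places the labelled fat at a meal that also carries three capsules: "This palmitic acid (20mg/kg body weight) is added to tomato juice and consumed at breakfast". Substrate oxidation is a listed endpoint under Outcome parameters, and fat oxidation is named in Objectives.

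**The concern.** In a crossover, the green tea minus placebo difference within a subject should reflect the extract and nothing else. Here the placebo filler is itself a fat, in a trial that measures fat oxidation. Swapping extract for oil makes fat intake a second difference between conditions, and its direction is known: placebo is higher.

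The protocol applies this kind of test elsewhere. Its Fat oxidation section defends the tomato juice partly because it is given in both conditions, so that its effect drops out of the comparison. That defence is not available for the capsule oil, which by the protocol's own description differs between conditions.

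At stake is the main effect of green tea on fat oxidation. If some of the additional oil is burned during the stay, placebo fat oxidation rises and the green tea effect looks smaller than it is. The imbalance is proportionally largest at breakfast, which is the smallest meal (20% of energy) and carries the tracer.

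**Working it through.** The plan gives no figure for capsule fat, so there is none to reproduce. The check bounds the difference.

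**Inputs from the protocol**
- Capsule mass 757 mg, three at breakfast and three at dinner (Protocol subsection).
- Named actives 84.5 mg EGCG + 2.1 mg caffeine = 86.6 mg per capsule (same place).
- Fat 33 En%, breakfast 20% of energy (Energy intake).
- Total energy expenditure on placebo 9538 kJ/day, on green tea 9867 kJ/day (Sample size, from the cited green tea extract study).

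**Assumptions not in the protocol**
- Energy intake equals 9538 kJ/day; range tried 7000 to 11000.
- Fat yields 37 to 37.7 kJ/g.
- The 757 mg is all fill, as the text implies.
- The thermic effect of fat is 0 to 3%.

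**Oil in the placebo**
- Per day: 6 × 0.757 = 4.54 g.
- Per capsule meal: 3 × 0.757 = 2.27 g.

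**Difference between conditions**
- Upper bound, if the green tea capsule holds no fat: 4.54 g/day. In energy, 4.54 × 37 = 168 kJ to 4.54 × 37.7 = 171 kJ.
- Lower bound, if everything except EGCG and caffeine is oil: 6 × 0.0866 = 0.52 g/day. In energy, 0.52 × 37 = 19 kJ, or just under 20 kJ at 37.7.

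**Relative to the diet, at 9538 kJ/day**
- Daily fat: 0.33 × 9538 / 37 = 85.1 g, or 83.5 g at 37.7 kJ/g.
- Share of daily fat: 0.52/85.1 = 0.6%, up to 4.54/83.5 = 5.4%.
- Breakfast fat: 0.20 × 85.1 = 17.0 g, or 16.7 g at 37.7 kJ/g.
- Share of breakfast fat: 0.26/17.0 = 1.5%, up to 2.27/16.7 = 13.6%.
- Dietary fat at the upper bound: (0.33 × 9538 + 168) / (9538 + 168) = 34.2 En%, against 33 planned.

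**Sensitivity to intake (37 kJ/g, upper bound of the difference)**

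| Intake, kJ/day | Share of daily fat | Share of breakfast fat |
|---|---|---|
| 7000 | 7.3% | 18.2% |
| 9538 | 5.3% | 13.3% |
| 11000 | 4.6% | 11.6% |

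**Effect on the primary parameter**
- Through the thermic effect of fat: at most 0.03 × 168 = 5 kJ/day.
- Planned difference: 9867 − 9538 = 329 kJ/day. The share is 5/329 = 1.5%.

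**Effect on the COMT contrast**
All four ethnicity-by-genotype groups take the same capsules. The same gram difference enters each group's green tea minus placebo result and cancels between groups, provided the fraction of the oil oxidised does not depend on genotype.

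**The case against.** The strongest reply is that the difference may be trivial. The active capsule's composition is in a product sheet not available here, and the possible range is almost nine-fold. The protocol says that lecithin, an emulsifier, is present in the capsules and uses one manufacturer's information for both types. That is compatible with an oil-based fill in both, which would pull the difference below the upper bound. This stands: 4.54 g/day is what the placebo contains, and a reader might wrongly take it as the difference between conditions.

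A reader might also infer that the capsule oil is left out of the diet calculation. The text does not say so. It neither includes nor excludes the oil, and the point rests on the absence of any capsule term in a section that otherwise sets out the calculation. That is a reason to add a sentence, not proof of an omission in practice.

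Third, the bias is conditional. Nothing in the protocol says how much of the extra oil would be oxidised before the stay ends at 07:00 on day 3, and half of each day's oil is taken at dinner. Nor does it allow any effect on recovery of the deuterium tracer to be worked out. The breakfast percentages show where the imbalance is concentrated; they do not measure bias.

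Finally, the respiratory quotient is a calculated quantity in Energy expenditure and substrate oxidation and is not a listed endpoint, so the point should be made for fat oxidation.

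None of this removes the core. Oil replaces extract, so the difference cannot be zero, its direction is fixed, and nothing in the protocol balances it.

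**Conclusion.** The point holds as a minor design improvement. The placebo is not fat-matched to the green tea capsule. The excess on placebo is between about 0.5 and 4.5 g/day (19 to 171 kJ). At an intake of 9538 kJ/day that is 0.6 to 5.4% of daily fat and 1.5 to 13.6% of breakfast fat. These percentages rest on the assumed intake and the energy value of fat; the gram bounds rest only on the protocol's capsule figures, read as fill weight.

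The bias in the green tea main effect on fat oxidation lies between zero and the full excess, and acts to understate that effect. The top end needs both a fat-free green tea capsule and complete oxidation of the extra oil within the stay.

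A reader might go further and conclude that the trial's main result is compromised. The documents do not support that: the effect on total energy expenditure is at most about 5 kJ/day, and the comparison between COMT groups is essentially untouched.

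**What to change.** In Energy intake, state the fat content of each capsule type from the product sheet and count it towards the fat and energy of breakfast and dinner in both conditions. Then adjust the fat in those meals so that capsules plus food supply the same fat and energy at both visits. One way is to add the missing amount of oil to the green tea-day breakfast and dinner. The capsules themselves stay as they are.

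The cost is a short menu calculation and weighing a few grams of fat per day. The meals are already prepared by a researcher in the research kitchen, and the protocol already leaves the researcher unblinded, so no further researcher blinding is lost. If the product sheet shows a difference near 0.5 g/day, stating that figure would largely settle the matter.
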